## Abstract

**Background:**

The strongest risk factor for depression is having a family history of the condition. Many individuals with a family history of depression are concerned about their personal risk for depression and report unmet educational and psychological support needs. No supportive and/or educational interventions are currently available that target this group of individuals. In this study we will develop and evaluate the first online psycho-educational intervention targeted to individuals with a family history of depression. Genetic risk information and evidence-rated information on preventive strategies for depression will be provided to such individuals in a general practice setting. The intervention will also incorporate a risk assessment tool. The content and delivery of the intervention will be pilot-tested.

**Methods/design:**

The proposed intervention will be evaluated in the general practitioner (GPs) setting, using a cluster randomized controlled trial. GP practices will be randomized to provide either access to the online, targeted psycho-educational intervention or brief generic information about depression (control) to eligible patients. Eligibility criteria include having at least one first-degree relative with either major depressive disorder (MDD) or bipolar disorder (BD). The primary outcome measure is 'intention to adopt, or actual adoption of, risk-reducing strategies’. Secondary outcome measures include: depression symptoms, perceived stigma of depression, knowledge of risk factors for development of depression and risk-reducing strategies, and perceived risk of developing depression or having a recurrence of family history. Over the course of the study, participants will complete online questionnaires at three time points: at baseline, and two weeks and six months after receiving the intervention or control condition.

**Discussion:**

This novel psycho-educational intervention will provide individuals with a family history of depression with information on evidence-based strategies for the prevention of depression, thus, we hypothesize, enabling them to make appropriate lifestyle choices and implement behaviors designed to reduce their risk for depression. The online psycho-educational intervention will also provide a model for similar interventions aimed at individuals at increased familial risk for other psychiatric disorders.

**Trial registration:**

The study is registered with the Australian and New Zealand Clinical Trials Group (Registration no: ACTRN12613000402741).

## Background

Having a family history of depression is the strongest documented risk factor for depression [1]. Family, twin, and adoption studies strongly suggest that both major depressive disorder (MDD) and bipolar disorder (BD) have heritable components [2], with heritability estimates of 40% for MDD [1,3] and 80% for BD [4,5].

A meta-analysis of family studies of MDD found a relative risk of 2.8 for MDD in first-degree relatives of affected probands, compared to control subjects [1], which is greater than all other reported risk factors. The presence of multiple relatives with MDD, as well as early age of onset, recurrence and severity of the depression in affected relatives, are factors that indicate an even higher familial risk [6]. The magnitude of familial aggregation for BD is extremely high; the relative risk in first-degree relatives of probands with BD compared to control cases has been estimated at 13.6 [7].

Genes that are responsible for an inherited susceptibility to depression are still the focus of intensive research efforts; genetic testing for susceptibility to mental health conditions is not available for clinical use. Given this, family history is currently the best predictor for the development of MDD and BD [6]. The role of family history as a key risk factor is undisputed, and epidemiological data can be used to provide people with a family history with estimates of their risk.

Many individuals with a family history of depression report unmet educational and psychological support needs in relation to a range of issues, including: estimating their personal risk of developing depression, as well as the risk to offspring; learning how depression can be prevented in those at increased risk based on family history, as well as early intervention and risk modification in young relatives; how to cope with family vulnerability; and reproductive decision-making [8,9]. Despite this well-documented endorsement of the need for psycho-educational interventions, no such interventions are currently available targeting this group of individuals.

Virtually nothing is known about the optimal approaches to providing risk information to people with a family history of depression. Professional guidelines suggest that genetic risk information should be offered to people with BD and their families, particularly those who are considering having children [10]. The following groups of individuals may benefit from risk information in particular: adult children, siblings and parents of affected individuals; affected individuals and their partners planning their families; and, affected people who maintain high-risk behaviors [11]. Indeed, as many as 75% of individuals with BD report that they would like expert advice about their genetic risk [12]. The guidelines, however, do not provide guidance on how to deliver the information.

Despite the potential value of information provision about familial risk, surveys of genetic counselors and psychiatrists show that they feel ill equipped to provide patients with such information [13-15]. Estimating the risks for the development of depression is challenging, given the lack of systematic reviews and meta-analyses available on more complex family relationships (e.g. risk associated with having a second-degree rather than first-degree relative with depression, presence of multiple affected relatives on either one side only or both sides of the family), and possible presence of a heterogeneous group of disorders within a given family.

Finally, further complexity is introduced through the contribution of environmental factors, which may be either familial or non-familial. Environmental familial factors pertain to the shared familial environment (e.g. parenting style), and environmental non-familial factors relate to the known contribution of sociodemographic variables, individual environmental (e.g. stressful life events) and health-related factors (e.g. presence of non-psychiatric chronic illness). It should, however, be noted that empirical risks reported by family studies (as distinct from adoption and twin studies) do not allow for a differentiation between familial genetic and environmental contributors to depression risk [1].

It is critical that information on familial risk for depression to individuals at increased risk is accompanied by the provision of advice on early detection, risk management and prevention. For example, individuals at increased familial risk should be advised to undergo regular screening by a health care provider in a timely manner, to capitalize on the predictive power of early warning signs and intervene preventively [16], in accordance with new prevention frameworks in psychiatry, which regard minor depression as a risk factor for MDD [17]. While several risk factors for depression, including family history, cannot be changed, individuals at increased risk are likely to benefit from accurate and up-to-date information on risk factors that are amenable to change and/or strategies they may adopt to reduce their risk. Such risk management strategies may either be based on evidence from randomized controlled trails (RCTs) (e.g. cognitive behavioral therapy [CBT], regular exercise) [18-22] or represent potential risk-reducing strategies that correspond to universally recognized standards for healthy living (e.g. avoiding illicit drugs and excessive consumption of alcohol, getting adequate sleep) [23-25].

Studies of individuals and families with BD suggest that patients and families often vastly overestimate the absolute risks of depression development in first-degree relatives [2,12]. Furthermore, in our previous work involving individuals from families with multiple cases of MDD and BD, we found that concerns about increased genetic risk strongly contributed to a reluctance to have children [9,26]. These data are of concern given that reluctance to have children may in part be likely based on overestimations of risks and suggest that psycho-educational interventions need to address inaccurate risk perceptions. Our prior work also ascertained the information needs of families with multiple members with depression [27]. The majority of people reported wished to obtain information directly from health professionals [27]. However, the need for additional information sources was also identified, and videos and accessing information through the internet were highly rated options.

While high-quality websites on depression are available in Australia (e.g. http://www.beyondblue.org.au, http://www.bluepages.anu.edu.au, http://www.blackdoginstitute.org.au) and internationally, they are not targeted to people with a family history of depression. In this study we will develop a world-first online, evidence-based psycho-educational intervention targeting people at increased risk for depression by virtue of their family history. The intervention will offer 'depression literacy’, including education on prevention and treatment strategies targeted to people with a family history of depression; it will not be designed to provide therapy to prevent or treat depression. The evidence for efficacy of such interventions has been illustrated: several high-quality online interventions that deliver therapy are already available (e.g. MoodGYM) [28]. Evidence is also available that an online intervention focused on depression literacy (e.g. BluePages) is as effective as online CBT (MoodGYM) in reducing the symptoms of depression [29].

The identification of people at increased risk for genetic conditions is particularly challenging because of the unique nature of shared DNA within families, generating implications for whole families rather than merely the individuals involved. Thus, family dynamics and communication patterns can play a major role in determining how information about genetic risk is shared within the family and how individual family members make decisions about, for example, reproduction, early detection and prevention of depression.

Depression with a hereditary component raises several unique issues which call for a sophisticated and rigorously tested approach to patient education. First, information on one’s familial susceptibility to a psychiatric disorder has the potential to impact on the individual’s sense of well-being and integrity and, in the most vulnerable cases, to precipitate the feared condition [30]. Another feature that is likely to compound the delivery of psycho-education is the stigma associated with psychiatric disorders [30,31]. In contrast to individuals with chronic physical conditions, those with psychiatric disorders are amongst the most highly stigmatized groups in society [32,32], regardless of the degree of genetic contribution. In our prior work we found that endorsement of a genetic model for depression was strongly correlated with perceived stigma, which suggests that having a genetic explanation for depression has the potential to further exacerbate the stigma associated with this condition [9]. These data show that a psycho-educational intervention needs to be highly sensitive to the challenges faced by people at increased hereditary risk for depression; our intervention, therefore, aims to provide accurate and realistic information about familial risk without increasing the perceived stigma associated with depression [34]. To address the unique challenges posed by depression with a hereditary component, this project employs a sophisticated analysis of the existing empirical findings on genetic risk for depression and a complex and rigorous methodology.

### Study objectives and hypotheses

This study aims to evaluate the first online psycho-educational intervention targeted to individuals with a family history of depression to provide such individuals in a general practice setting with genetic risk information and evidence-rated information on preventive strategies for depression. The intervention to be tested incorporates a risk assessment tool, delivery of education targeted to people with a family history of depression and feedback to general practitioners (GPs) of individuals’ risk status. It will be evaluated in the GPs setting using a cluster RCT.

The primary aim of the study is to determine whether the intervention, compared to the control condition, leads to both greater intention to adopt, and actual adoption of, risk reduction strategies for depression in people at increased familial risk. The secondary aims are to evaluate whether the intervention will lead to: lower levels of depression symptoms and perceived stigma, and better knowledge about genetic and environmental risk factors for depression and efficacy of risk reduction strategies.

The study will test the following hypotheses: compared to a control group of people receiving brief generic information about depression, people receiving the targeted psycho-educational intervention will be more likely to: (i) intend to adopt, and actually adopt, risk reduction strategies for depression; (ii) have lower levels of depression; (iii) have lower perceived stigma related to depression; and (v) possess better knowledge about risk factors and risk reduction strategies for depression, two weeks and six months post-intervention.

### Design

This cluster RCT will be conducted in a general practice setting in the state of New South Wales, Australia. The study protocol adheres to the CONSORT guidelines [35]. The study design is presented in Figure 1. GP practices will be randomized to provide either access to the online targeted psycho-educational intervention or brief generic information about depression to eligible patients. We decided against an 'attention placebo’ group (e.g. another depression website not targeted to people at high risk for depression) as this would lead to control group participants accessing variable and heterogeneous amounts of education. Instead, participants attending a GP randomized to the control group will receive brief generic information about depression, produced by *beyondblue* (national depression network), i.e. 'Understanding depression’. Randomization by participating GP practice will be undertaken centrally using a computer-based randomization program. Thus the unit of randomization will be the GP practice, not the individual participant. This design will optimize the use of the intervention and minimize contamination between participants attending the same GP; if individual participants rather than GPs were randomized, the approach of the doctor to controls could change due to the doctor’s experience with the tool.

**Figure 1 F1:**
[figure not shown]
Study design and flow of participants through study.

### Study procedures

Researchers will work with staff at GP practices to generate random lists of up to 500 patients per practice who meet eligibility criteria (i) to (iii) above and have attended the practice in the last two years. GPs will be asked to screen these randomly selected patients and exclude those who would not be suitable (e.g. cognitive impairment, severe illness, patients with a psychiatric disorder that is currently not well controlled); those deemed suitable will be sent a letter of invitation by their GP. Potential participants will be blinded to their intervention assignment in that they will be told that the study is comparing different types of educational interventions. There will be two separate secure study websites, one with the intervention and one with the control condition. The letter of invitation will direct interested individuals to the appropriate study website according to GP randomization. Participants will opt-in and be asked to provide a current e-mail address; participants will then receive a unique username and password that will enable them to access the appropriate website.

Each participant entering the websites (both intervention and control) will complete the *Family History Screen (FHS)*[36] to confirm eligibility (in particular whether they have a first-degree relative with MDD or BD) and provide the basis for feedback to the participants and optionally their GP regarding their family history details (intervention group only), including whether they have had an episode of MDD or BD and brief details regarding their family history. Ineligible individuals will be thanked and asked to discontinue participation, while eligible participants will proceed to complete the baseline questionnaire. The *FHS* is a valid and reliable measure of psychiatric family history and has been shown to have high sensitivity and specificity for depression [36]. It identifies the status of the biological first-degree relatives for assessment (pedigree collection) and screens lifetime history of MDD and/or BD of the participant and the biological relatives identified in the pedigree. The *FHS* begins with a broadly sensitive introductory question about the participant and any first-degree family member to stimulate memory. If the status of any family members is provided in response to the first question, an additional five narrower 'symptom definition’ questions are asked.

### Measures

#### Socio-demographic data

At baseline, data on sex, age, highest level of education achieved, current marital status and country of birth will be collected.

#### Outcome measures to be administered at all time points

##### Patient health questionnaire depression (PHQ9)

The *PHQ9* is a ten-item self-administered validated instrument, which scores each of the Diagnostic and Statistical Manual of Mental Disorders (DSM-IV) criteria for MDD [37]. It can be used both as a diagnostic measure as well as a symptom severity measure and assesses depression symptoms over the past two weeks. It has 4-point Likert type response options ranging from “Not at all” to “Every day”; scores range from 0 to 27, with higher scores indicating higher levels of depression. Depression levels can be categorized as mild (5 to 9 scores), moderate (10 to 14 scores), moderately severe (15 to 19 scores) or severe depression (20 to 27).

##### Knowledge of risk factors for development of depression and risk-reducing strategies

10 items have been purposively designed to assess knowledge of the: (i) genetic and environmental risk factors for depression development and (ii) efficacy of a range of prevention strategies that are covered in the intervention. Item wording is shown in list below. A score of one will be given for each correct answer and a score of zero for an incorrect or “don’t know” response. Total knowledge score will be calculated by summing the correct responses (range 0–10).

##### Perceived susceptibility to major depressive disorder and bipolar disorder

Two items adapted from a previous study [40] will assess: participants’ perceived risk of “developing (or having a recurrence of) MDD” and “developing (or having a recurrence of) BD” compared to an “average person of the same age and gender”, using Likert-scale response options ranging from 1 (“Much lower”) to 5 (“Much higher”).

##### Intention to adopt, and actual adopting of, risk-reducing strategies

Eight items will be used to measure participants’ intention to adopt, and actual adoption of a range of 'risk-reducing strategies’ that were covered in the intervention; only strategies for which at least some evidence of efficacy (prospective data or stronger evidence) is available will be included in this measure. Response options include: “No, and I do not intend to in the next six months” (0), “No, but I intend to in the next six months” (1), “No, but I intend to in the next 30 days (2)”, and “Yes, I have been, but for less than six months” (3), and “Yes, I have been for more than six months” (4). Scores for each item represent the five stages of change: Pre-contemplation (0), Contemplation (1), Preparation (2), Action (3), and Maintenance (4) [41,42]. For analyses, a total mean score will be calculated (range 0 to 4) to assess individuals’ intention and actual adopting of risk-reducing strategies. In addition, for each strategy where participants indicated “Yes”, they will also be asked “how successful they have been” in implementing the strategy. Four-point Likert-type response options will be used, ranging from "Slightly successful" to "Completely successful".

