### Control

Following completion of the baseline questionnaire, control group participants will be directed to a PDF of a brief generic pamphlet on depression produced by *beyondblue* (National Depression Network), 'Understanding depression’, which includes information about common symptoms of depression, criteria used to diagnose depression and treatments available. Following completion of the six-month survey, control group participants will be provided with access to intervention.

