### Statistical methods

Analysis for the dichotomous primary outcome, intention to adopt risk-reducing strategies, will be performed using the generalized linear mixed model, which extends the standard logistic regression model to allow for clustered data. The continuous outcome of *PHQ9* will be analyzed using the linear mixed model. Adjustment for any potential confounding variables (such as age, sex, type of family history) will be made if there is important baseline imbalance in these variables between intervention groups.

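### The 0–4 adoption score separates behaviour kept under and over six months, but follow-up ends at six months, so the top step mostly records prior habit, elapsed time or reply date rather than new adoption

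*Protocol article*

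**What the plan says.** In the protocol article, the Measures subsection on intention to adopt and actual adopting of risk-reducing strategies gives each of eight items five ordered answers. Score 3 (Action) is "Yes, I have been, but for less than six months" and score 4 (Maintenance) is "Yes, I have been for more than six months". The same subsection states that for analyses "a total mean score will be calculated (range 0 to 4) to assess individuals’ intention and actual adopting of risk-reducing strategies".

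The abstract (Methods/design) sets the questionnaires "at baseline, and two weeks and six months after receiving the intervention or control condition". The hypotheses use the same two follow-up times. The Control section closes the randomised comparison there: "Following completion of the six-month survey, control group participants will be provided with access to intervention".

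The abstract names the construct as primary: "The primary outcome measure is 'intention to adopt, or actual adoption of, risk-reducing strategies". The Statistical methods section, however, describes a binary endpoint: "Analysis for the dichotomous primary outcome, intention to adopt risk-reducing strategies, will be performed using the generalized linear mixed model". The article does not say how scores 3 and 4 are classed in that binary version.

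**The concern.** The primary aim is causal: does the intervention produce more intention to adopt, and more actual adoption, than the control pamphlet? A scale for that aim should move when someone newly takes up a strategy and stay still when nothing has changed.

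The step from 3 to 4 does neither well. Its boundary falls at the length of the follow-up, so a newly adopted strategy can hardly cross it, while one begun shortly before enrolment crosses it by being continued. In the mean, that crossing earns the same credit as moving from Preparation (2) to Action (3), which is the change the trial is looking for.

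At stake is how well the score detects new adoption, and how a difference in mean score is read.

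**Working it through.** **The plan's own figure.** The article claims 80% power for 20 practices of 12, ICC 0.06, 50% against 72%. I assume 1:1 allocation and two-sided alpha 0.05, as the article states neither.
- Design effect: 1 + (12 − 1) × 0.06 = 1.66.
- Effective number per arm: 120 / 1.66 = 72.3.
- Standard error (unpooled): √[(0.50 × 0.50 + 0.72 × 0.28) / 72.3] = 0.079.
- Power: Φ(0.22 / 0.079 − 1.96) ≈ 79.5%.

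The claim is reproduced to within rounding. A pooled variance gives 78.0%, and a t reference with 18 degrees of freedom gives 74.9%. None of these figures uses the 0–4 score, so the sample size does not turn on this point.

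**Response options against the schedule.** Inputs are the five answers and eight items (Measures), and follow-up at two weeks and six months (abstract).

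| Stage of a strategy at baseline | Two weeks | Six months |
|---|---|---|
| 0–2, taken up after the intervention | at most 3 | 3 if answered on time; 4 if begun early and answered late |
| 3, continued | usually 3 | 4, by elapsed time |
| 4, continued | 4 | 4, no room to rise |

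A strategy begun on or after the day of the intervention has lasted at most two weeks at the first follow-up and about six months at the last. A strategy at 3 at baseline was already under way, so at a survey six months later it has lasted more than six months if it was kept up. A duration of exactly six months fits neither wording.

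**Size on the 0–4 mean.**
- One strategy moving from 3 to 4 adds 1/8 = 0.125 to a participant's mean. Three add 3 × 0.125 = 0.375.
- If a share q of all participant-strategies is at 3 at baseline and continued, the group mean rises by q × 1 through time alone: 0.05, 0.10, 0.20 and 0.30 for q = 5%, 10%, 20% and 30%. The article gives no stage distribution, so q is assumed.
- For a strategy begun in week 1, a late reply is likewise worth 0.125. The outer bound, all eight begun in week 1, is 3.0 on time against 4.0 late; this is an extreme case.

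**Room left for new adoption.** Let p be the share of participant-strategies already adopted (3 or 4) at baseline, and suppose these contribute no difference between arms. The overall difference is then (1 − p) times the difference among the rest, so the latter must be 1/(1 − p) times the overall difference sought: 1.43, 2.0 and 3.33 for p = 30%, 50% and 70%. These values of p are also assumed. Several items are everyday habits (sleep, diet, social support, positive attitude), and people with a previous episode are eligible, so a sizeable p is plausible but not documented.

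**The binary outcome.** If 3 and 4 fall on the same side of the cut-point, the drift and late-reply effects vanish. If both count as success, strategies in place before the trial still count as success.

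**The case against.** The strongest reply has five parts.

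1. *The powered test is a proportion, and no analysis of the mean is named in the Statistical methods section.* This stands as a limit on scope. It does not remove the point, because the Measures section says the 0–4 mean is calculated for analyses and the cut-point for the proportion is not given.
2. *Drift and prior habits affect both arms alike.* Correct in expectation. A reader might infer a biased treatment comparison, but the documents do not support that: nothing in them suggests that reply delay or baseline stage differs by arm. With 20 practices a chance imbalance in baseline stage is possible, no more.
3. *A 4 can be an intervention effect.* Also correct. A reader might infer that the trial cannot show Maintenance as an effect at all. But a participant at 3 reaches 4 only by not lapsing, and one at 4 stays there only by not lapsing. If the intervention helps people persist, the resulting difference in 4s is a genuine randomised effect. It is persistence, though, and the aim is adoption.
4. *The magnitudes rest on assumed distributions.* True. Moreover, the items ask about behaviour undertaken in order to lower depression risk, so not every long-standing habit need score 4.
5. *The five levels are an established stages-of-change scheme, and baseline adjustment may sit in an analysis plan that is not shown.* Fair. The scheme is sound as description, and missing detail on adjustment is not itself the complaint. What the article does fix is a score whose top step does not fit its follow-up.

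**Conclusion.** The timing conflict is in the text and the point holds for the 0–4 mean. Within the randomised follow-up, new adoption can reach 4 only through a late answer to the six-month survey, a continued baseline 3 gains 0.125 on a participant's mean without any change in behaviour, and a baseline 4 has no room to improve. The consequence is noise, a ceiling and reduced sensitivity to new adoption. How much sensitivity is lost cannot be computed, because the article gives neither a stage distribution nor a standard deviation.

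Bias is conditional on a difference between arms in reply delay or baseline stage. For the dichotomous outcome the 3/4 split matters only if the cut-point separates the two levels. The stated sample size is unaffected. The change is worth making because it is cheap and brings the score into line with the primary aim.

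**What to change.** For the arm comparison, state that:

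- Action and Maintenance are scored as one adopted level (maximum 3) at all time points;
- the model adjusts for the baseline score;
- actual adoption is also reported as the proportion newly adopted among participant-strategies scored 0–2 at baseline, allowing for clustering by practice and by participant;
- the five-stage score is kept as description.

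For the dichotomous outcome, state on which side scores 3 and 4 fall.

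The parts do different work. Merging 3 and 4 removes the drift and late-reply effects but not the ceiling: strategies adopted before the trial stay at the maximum, and those at 3 now also have no room to rise. The baseline adjustment and the new-adoption analysis deal with prior habits.

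The cost is analysis wording only. The measure is listed for all time points, and the baseline questionnaire is completed before either condition is delivered. There are two downsides: the arm comparison no longer credits the duration of existing habits, and the new-adoption analysis leaves out any effect on persistence, which the descriptive five-stage table can still show. Power for the new-adoption analysis cannot be given from the article and should be checked once the baseline stage distribution is known, without reference to outcome by arm.

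### The 0–4 mean mixes intention with behaviour, and no stated summary isolates the actual adoption named in the primary aim

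*Protocol article*

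**What the plan says.** In the protocol article, *Study objectives and hypotheses* states the primary aim as whether the intervention "leads to both greater intention to adopt, and actual adoption of, risk reduction strategies for depression in people at increased familial risk". Hypothesis (i) repeats both parts, for two weeks and six months after the intervention.

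Under *Measures*, the section on intention and adoption begins: "Eight items will be used to measure participants’ intention to adopt, and actual adoption of a range of" strategies. Each item is coded by stage of change. Code 0 is no intention, codes 1 and 2 are intention without behaviour (within six months and within 30 days), and codes 3 and 4 are behaviour (for less than and for more than six months). The stated derivation is that "a total mean score will be calculated (range 0 to 4) to assess individuals’ intention and actual adopting of risk-reducing strategies". Each yes answer also prompts a question on how successful the person has been; no analysis of that question is described.

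Other sections describe the primary outcome differently. The Abstract words it as intention or adoption. *Sample size and statistical power* names intention alone and works with a proportion, 50% in the control arm and a 22-point difference. *Statistical methods* gives a generalized linear mixed model for a dichotomous intention outcome and describes no model for the 0–4 mean.

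**The concern.** The codes are ordered within one strategy: doing it scores more than planning it. Averaging over eight strategies removes that protection, because several intentions can add up to as much as, or more than, several adoptions. A higher mean in the intervention arm is therefore compatible with no extra behaviour at all.

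What is at stake is the second half of the primary aim. If the mean rises and is reported as support for the hypothesis that people actually adopt strategies, the claim may rest on stated plans alone. This matters most at six months, when uptake after the intervention has had time to show. The dichotomous outcome does not fill the gap, since it is described as intention only.

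**Working it through.** **1. What the plan's power figure covers.** Inputs from *Sample size and statistical power*: 20 practices, 12 participants each, ICC 0.06, 50% against 72%. Assumed, because not stated: equal allocation and two-sided alpha 0.05.

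- Design effect = 1 + (12 − 1) × 0.06 = 1.66.
- Effective number per arm = 120 / 1.66 = 72.3.
- SE = √[(0.50 × 0.50 + 0.72 × 0.28) / 72.3] = 0.079.
- Power = Φ(0.22 / 0.079 − 1.96), about 79.5%, in line with the stated 80%.

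The power figure is not in dispute. It belongs to a proportion intending, not to the 0–4 mean and not to adoption.

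**2. The score.** Let n1 to n4 be the numbers of strategies answered at codes 1 to 4.

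- Mean = (n1 + 2·n2 + 3·n3 + 4·n4) / 8. With all items at 0 this is 0; with all at 4 it is 32/8 = 4, which matches the stated range.
- Strategies adopted = n3 + n4.

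**3. Three response patterns.**

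| Pattern | Sum | Mean | Adopted (3–4) | Intended or adopted (1 or more) |
|---|---|---|---|---|
| A: all eight intended within 30 days | 8 × 2 = 16 | 2.0 | 0 | 8 |
| B: five newly adopted, three not intended | 5 × 3 = 15 | 1.875 | 5 | 5 |
| C: four kept up for over six months, four not intended | 4 × 4 = 16 | 2.0 | 4 | 4 |

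A ranks above B and level with C, although A has adopted nothing.

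**4. How far the example reaches.** It needs its conditions.

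- If A's intentions are only for the next six months, A scores 8/8 = 1.0.
- If one of B's five has been kept up for over six months, B scores (4 × 3 + 4)/8 = 2.0 and ties with A.
- If one of B's other three is intended within six months, B scores (15 + 1)/8 = 2.0 and again ties.
- Five strategies all kept up for over six months score 20/8 = 2.5.

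The general point does not need the example. Enumerating all response patterns, a mean of 1.5 is compatible with 0 to 4 strategies adopted, and a mean of 1.875 or 2.0 with 0 to 5. For an individual, a mean above 2.0 does imply at least one adopted strategy, because eight intentions cannot exceed 8 × 2/8 = 2.0.

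**5. Differences between arms.** With n3 and n4 held fixed, the change in the mean is (Δn1 + 2·Δn2)/8.

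- Moving one strategy from 0 to code 2 adds 2/8 = 0.25 with no behaviour change.
- Going on from code 2 to doing it (code 3) adds only 1/8 = 0.125.
- Moving all eight from 0 to 2 adds 2.0, half the scale, with adoption still at zero.

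**The case against.** The strongest reply is that the 0–4 mean is not clearly the primary analysis variable. *Sample size and statistical power* and *Statistical methods* work with a dichotomous intention outcome, and no model for the mean is set out. *Sample size and statistical power* also acknowledges that intentions are only an indirect measure of behaviour and gives reasons for choosing them. This stands: one cannot say that the trial's primary test will be a comparison of these means. It does not rescue the adoption half of the aim, because the dichotomous outcome is described as intention only.

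Second, a mean of ordered stages is a recognised kind of summary of progress towards behaviour, and any composite lets items offset one another. That is a fair reason to keep the mean as an overall stage score. It is not a reason to read the mean as evidence of adoption.

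Third, adoption is recorded item by item, and a count of adopted strategies is something a full protocol or analysis plan could add. The first part is correct and limits the criticism to the summary. On the second, this is not a case of silence: the article itself fixes a derivation and says that it assesses both constructs.

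Fourth, the ranking example is selective. It is, and its conditions are listed in the working. They are not far-fetched, since a strategy begun after the intervention can have run for only about two weeks or six months at follow-up and would mostly be coded 3.

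**Conclusion.** The concern holds for the summary score. The primary aim includes actual adoption; the one stated summary that covers adoption can rise through intentions alone; and the other stated outcome addresses intention only. The scoring results (2.0 with none adopted, 1.875 with five adopted) follow directly from the published codes and need no assumption beyond the response patterns shown.

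A reader might infer more than this:

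- *That the trial's data cannot show adoption.* The documents do not support this, because codes 3–4 separate adoption from intention at every time point.
- *That the primary result will be a misleading difference in means.* The analysis section describes a dichotomous outcome, so this is not established.
- *That the distortion has a known size.* The article gives no distribution of answers over the stages and no correlation between items. A figure in standard deviations would rest on invented inputs: with one assumed distribution (30/15/10/10/35% for codes 0 to 4), the SD of the mean is about 0.60 if items are independent and about 1.05 if they correlate at 0.3.

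The change is worth making before analysis, because an adoption count chosen afterwards would be chosen with results in view.

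**What to change.** - Keep the 0–4 mean, if wanted, as an overall stage score, and describe it as that.
- From the same eight items, prespecify the number of strategies adopted (score 3 or 4). Compare it by arm at six months with a model that allows for clustering by practice.
- State that actual adoption will be claimed only if this count favours the intervention; otherwise limit the conclusion to intention or overall stage.
- Do not use intention among strategies not adopted as an outcome. It depends on adoption after randomisation and falls when intenders become adopters: someone who moves from 3 intended and 2 adopted to 1 intended and 4 adopted would show a drop from 3 to 1. If a companion measure is wanted, use the number of strategies intended or adopted (score 1 or more), which stays at 5 here while the adoption count rises from 2 to 4.
- Make the Abstract, the objectives, the measure's description, the sample size section and the statistical methods agree on which variable is primary.

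The cost is one or two derived variables and models on data already collected. The small downside is a more demanding condition for claiming adoption.
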